## **Detailed calculations of power for the diarrhoea and secondary outcomes:**

### **I. POWER OF THE TRIAL FOR THE DIARRHEAL OUTCOME.**

#### 1. Period Prevalence (i.e. proportion of children with $\geq 1$ episode of moderate-severe diarrhoea over the 12 weeks intervention period)

Based on previous data from the case-control GEMS (Global Enteric Multicentre Study) for the Basse (Upper River BHDSS) region in the Gambia, the background point prevalence of moderate-severe diarrhoea in children under 3 years of age can be as high as 14%, whereas data from the same region in a previous survey HUAS (Health Care Utilization and Attitudes Survey) showed that this number can be as high as 20%.

For our calculations, we chose to consider 15% as the proportion of children with at least one episode of diarrhoea in the IHAT group over the 12 wk. intervention period, which we hypothesise would be similar to the background period prevalence. This prevalence is similar to that found in other iron intervention studies for the no-iron groups (7, 8).

The graph below shows the power of the trial (200 patients per arm at a 10% one-sided type I error rate) to detect a significant difference between IHAT and ferrous sulphate (FS) as the ferrous sulphate diarrhoea period-prevalence varies:

[figure not shown]

For a period prevalence of 0.15 in the IHAT arm and 0.25 in the ferrous sulphate arm, the power of the trial is around 90%. We note that previous data for ferrous sulphate suggest that 25% is a reasonable figure for the period prevalence: for example Zlotkin et al 2013 reported this to be 16.8% in the iron group and Jaeggi et al 2014 reported 27.3%. Furthermore, for the Gambia specifically, preliminary data from the 84 days period of the current HIGH study in the Soma region shows that, during the 84-days of the intervention, moderate-severe diarrhoea was recorded at least once as an adverse event in 36% of the children.

For comparing placebo and IHAT, we used a non-inferiority approach. With 200 patients per arm, we would have 93% power to show non-inferiority of IHAT with a 10% non-inferiority margin (at a 10% one-sided type I error rate). This means that, if the true diarrhoea period prevalence in the IHAT and placebo arms is 0.15, this sample size has 93% power to show that the upper confidence interval of the difference in prevalence between these two arms is less than 10%.

2. Incidence density (i.e. number of moderate-severe diarrhoea episodes per child over the 12 weeks intervention)

Preliminary data from the 84 days data collected in the HIGH study in the Soma region in the Gambia suggest that the incidence density of moderate-severe diarrhoea is 1.28 episodes per child over the 84-days study period. Using the same type I error rate and sample size as above, the graph below shows the power of the trial to detect a significant difference between arms as the rate ratio varies.

[figure not shown]

For a rate ratio of 0.8 (i.e. IHAT provides a 20% reduction in mean incidence density of moderate-severe diarrhoea relative to ferrous sulphate), the power is almost 90%.

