#### **There are four null hypotheses in the study:**

- 1) non-inferiority of IHAT compared to ferrous sulphate for efficacy (in terms of Hb and iron deficiency correction: i.e. IDA) response probability (or prevalence). In this case we are testing the null hypothesis that: response in the IHAT arm minus the response probability in the ferrous sulphate arm is less than or equal to  $-0.1$ . We define 'response' for IDA as correction of iron deficiency and either achieving a normal Hb or an increase of at least 1 g/dL after 12 weeks of iron supplementation.
- 2) superiority of IHAT compared to ferrous sulphate in terms of incidence density of diarrhoea. Here the null hypothesis is that the mean number of new episodes in the IHAT arm is greater than or equal to the mean number in the FeSO4 arm.
- 3) superiority of IHAT compared to ferrous sulphate in terms of prevalence of diarrhoea. Here the null hypothesis is that the prevalence of diarrhoea in the IHAT arm is greater than or equal to the prevalence in the FeSO4 arm.
- 4) non-inferiority of IHAT compared to placebo in terms of prevalence of diarrhoea. Here the null hypothesis is that the prevalence of diarrhoea in the placebo arm minus the prevalence in the IHAT arm is less than or equal to  $-0.1$ .

Because this is a pilot study we do not formally adjust for multiple testing due to the four hypotheses. This is because any significant results will be tested again in a pivotal study.

The trial is powered to show non-inferiority of IHAT relative to ferrous sulphate for the 12 weeks efficacy response probability. At the 12 weeks time-point (i.e. Day 85), the estimated odds ratio between the IHAT and FeSO4 arms will be calculated, together with a 90% one-sided confidence interval. If the lower limit of the confidence interval for this difference is above 0.583 (equivalent to a 10% absolute difference if FeSO4 response rate is 0.3), then non-inferiority of IHAT in terms of efficacy will be declared.

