Because many trials conducted in Africa and other developing countries with the gold standard ferrous sulphate or ferrous fumarate supplementation still fail to provide anaemia resolution in interventions shorter than 6 months, we have considered here that an increase of 1 g/dl in Hb after 3 months is an indication of efficacy, even though we accept that this is not clinical efficacy. We have based our assay sensitivity from data published with relevant iron supplement studies in children available in the literature (3, 7, 52). We plan, however, to use the data collected in the proposed study to conduct an exploratory analysis to test for assay sensitivity. These data will be very useful so that adequate treatment effect sizes can be used to power any future studies, in particular a pivotal trial, both for ferrous sulphate and IHAT supplementation effects.

Due to this trial being a pilot study, any significant results will be re-tested in the pivotal 'full' trial (BMGF full award). Thus, we considered a larger than traditional type-I error rate of 10%. Assuming that 30% (i.e. a response probability of 0.3) of the children in both arms will resolve iron deficiency and either achieve a normal Hb or an increase of at least 1 g/dL after 12 weeks of iron supplementation (3, 7, 52), then a sample size of 200 in the IHAT arm and 200 in the ferrous sulphate arm will provide 89% power to show non-inferiority with a non-inferiority margin of 0.1 (0.583 on the odds-ratio scale). In other words, the trial will have 89% power (at a 10% one-sided significance level) to show that the lower boundary of the confidence interval of the odds ratio between IHAT and ferrous sulphate is more than 0.583 at 12 weeks.

We have based our calculation above on assay sensitivity data taken from other studies with iron supplements reported in the literature, but we will also perform an exploratory analysis to test for assay sensitivity, and this information will be used to power the potential future pivotal study.

We have considered two options for modelling the diarrhoea outcome: 1) 'period prevalence', i.e. the proportion of children with at least one episode of moderate-severe diarrhoea over the 12 weeks intervention period; 2) 'incidence density'. i.e. the number of new diarrhoea episodes per child over the 12 weeks intervention period. The modelling of how the power of the trial varies according to assumptions for each of these outcomes is detailed below.

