The trial sample size will also provide 90% power to show superiority of IHAT in terms of moderate-severe diarrhoea 'incidence density', assuming that IHAT provides a 20% reduction in mean moderate-severe diarrhoea 'incidence density' relative to ferrous sulphate; and 90% power to show superiority of IHAT in terms of 'period prevalence' of moderate-severe diarrhoea, assuming that 25% of children will develop moderate-severe diarrhoea episodes with ferrous

sulphate and 15% will have moderate-severe diarrhoea with IHAT over the 12 weeks intervention. For the comparison between the IHAT and placebo arms, the trial is powered to show non-inferiority of IHAT relative to placebo, for example, the trial will have 93% power for the moderate-severe diarrhoea 'period prevalence' outcome. All the assumptions for these calculations were based on data from studies conducted in The Gambia for the same age group, please refer to the extra information below for further details.

As part of the rationale for the study is to provide information for a pivotal study, we also examined the precision that the sample size would provide on the confidence interval width of the outcomes considered. Since the width of the confidence interval is highly dependent on the proportion in the control group as well as the true odds ratio, we consider several different values in the table below.

| Binomial proportion in control group | True odds-ratio | 95% confidence interval width |
|--------------------------------------|-----------------|-------------------------------|
| 0.1                                  | 0.5             | 0.85                          |
|                                      | 1               | 1.38                          |
|                                      | 1.5             | 1.91                          |
| 0.3                                  | 0.5             | 0.49                          |
|                                      | 1               | 0.88                          |
|                                      | 1.5             | 1.27                          |
| 0.5                                  | 0.5             | 0.42                          |
|                                      | 1               | 0.80                          |
|                                      | 1.5             | 1.21                          |

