## 8.2 Statistical analysis

The data analysis plan will be fully developed prior to database lock and will be done with the expert input from [name] of the MRC Biostatistics Unit in Cambridge. Briefly, for the primary analysis, we will fit a logistic regression to the efficacy outcome data, adjusting for the strata created by age and Hb level groups prior to enrolment. The odds ratio for effect of IHAT relative to ferrous sulphate will be estimated, and if the lower 90% one-sided confidence interval is above 0.583 (equivalent to the 10% non-inferiority margin above), non-inferiority will be declared for IHAT. The diarrhoea endpoint will be analysed in a similar way, but tested for superiority (i.e. if the one-sided p-value for the Wald test of the effect of IHAT is less than 0.1) for the comparison between IHAT and ferrous sulphate. For the primary non-inferiority hypothesis we will conduct per-protocol and intention-to-treat analyses and for the superiority hypotheses we will conduct intention-to-treat analyses.

The secondary endpoints (calprotectin, NTBI etc) will be tested using linear regression with the same covariates. Morbidity data will be analysed using multiple regression analysis controlling for possible confounders.

In relation to the microbiome data analysis we will work together with our collaborators in the Sanger Institute and use the most up to date bioinformatics methodology available at the time of data analysis to investigate the impact of treatment arm and time in the composition of the gut microbiome. Since this analysis will only occur in late 2018/early 2019, it is premature to decide the strategy for data analysis now as this is a fast moving field with new and better bioinformatics tools becoming available every couple of months. The Sanger Institute works very closely with the European Bioinformatics Institute (EBI) (housed in the same campus) to ensure they use the very latest tools in their microbiome analysis.

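### The 90% power stated for the primary incidence-density test (H2) needs a Poisson count with mean 1.28, which the protocol's own 36% prevalence from the same study rules out; reconciled either way, power is roughly 40–55%

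*Supplement*

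**What the plan says.** All references are to the latest protocol version in the Supplement.

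- Section 8.1 lists as its second hypothesis "superiority of IHAT compared to ferrous sulphate in terms of incidence density of diarrhoea", stated on the mean number of new episodes per child.
- The summary of power in Section 8.1 reads: "The trial sample size will also provide 90% power to show superiority of IHAT in terms of moderate-severe diarrhoea" incidence density, for a 20% reduction relative to ferrous sulphate.
- The detailed calculation (part I, item 2, Incidence density) takes its mean from the HIGH study, whose preliminary data "suggest that the incidence density of moderate-severe diarrhoea is 1.28 episodes per child over the 84-days study period". At a rate ratio of 0.8 it concludes, for the 20% reduction "relative to ferrous sulphate), the power is almost 90" percent. It gives no variance or overdispersion assumption; the power curve itself is a figure we cannot see.
- Level and size carry over from the preceding item: "200 patients per arm at a 10% one-sided type I error rate". The choice of level is explained by the pilot nature of the trial: "Thus, we considered a larger than traditional type-I error rate of 10" percent.
- Item 1 (Period prevalence), on the same HIGH study and the same 84 days, says that "moderate-severe diarrhoea was recorded at least once as an adverse event in 36% of the children". It plans H3, the period-prevalence comparison, with 25% affected on ferrous sulphate and 15% on IHAT.
- Section 8.2 outlines a logistic regression for efficacy and adds: "The diarrhoea endpoint will be analysed in a similar way, but tested for superiority". It leaves the detail to a data analysis plan, to be completed before database lock, which is not shown.

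**The concern.** A mean count and a proportion with at least one event are tied together once a distribution is chosen. A mean of 1.28 with only 36% affected means 1.28/0.36 = 3.56 episodes per affected child. That is far more clustering than a Poisson count allows, and clustering inflates the variance of the mean. A power figure built on Poisson variance at 1.28 is then too high. The other possibility is that 1.28 is not the mean per child, in which case the calculation starts from the wrong rate.

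H2 is a primary hypothesis, and the trial is meant to inform a pivotal study. A non-significant H2 would be read as the outcome of a 90%-powered test, and the planning figure could be carried forward.

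**Working it through.** **Inputs (Section 8.1):** n = 200 per arm; one-sided level 0.10, so z = 1.2816; rate ratio 0.8, so |ln 0.8| = 0.2231; mean 1.28; proportion affected 0.36; planned proportions 0.25 and 0.15. The variance is not stated, so it is the assumption varied below.

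**Formula:** Wald test on the log rate ratio, power = Φ(0.2231/SE − 1.2816), with SE² = (v₀/m₀² + v₁/m₁²)/200.

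**1. Reproducing the stated figure.** Under Poisson, v = m.
- Ferrous sulphate 1.28, IHAT 1.024: SE = √(1/256 + 1/204.8) = 0.0938; power = Φ(2.380 − 1.282) = 86%.
- Variance at 1.28 in both arms: SE = √(2/256) = 0.0884; power 89%.
- IHAT 1.28, ferrous sulphate 1.6: SE = √(1/256 + 1/320) = 0.0839; power 92%.

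These bracket both statements in the protocol, so the figure is a Poisson result.

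**2. What Poisson implies.** P(at least one episode) = 1 − e^(−1.28) = 72%, against 36% reported.

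**3. Keeping both 1.28 and 36%.** The two figures are placed in the ferrous sulphate arm, which is where the protocol uses the 36%.
- *Negative binomial:* solve (1 + 1.28/k)^(−k) = 0.64, giving k = 0.243. Variance = 1.28 + 1.28²/0.243 = 8.01, or 6.3 times the mean. SE = √[(1/1.28 + 1/1.024 + 2/0.243)/200] = 0.223; power = Φ(0.999 − 1.282) = 39% (simulation 39%).
- *Zero-inflated Poisson:* solve λ/(1 − e^(−λ)) = 3.56, giving λ = 3.44. Variance = 1.28 × (1 + 3.44 − 1.28) = 4.05, or 3.2 times the mean. If IHAT lowers the number of episodes per susceptible child, SE = 0.160 and power is 54%. If it lowers the proportion susceptible, power is 51%.
- *Smallest possible variance:* every affected child has 3 or 4 episodes. Variance = 0.36 × (0.444 × 9 + 0.556 × 16) − 1.28² = 4.64 − 1.638 = 3.00, or 2.35 times the mean. With 36% affected in the IHAT arm too, its minimum variance is 1.91; SE = 0.135 and power is 64%. With the variance-to-mean ratio held at 2.35 in both arms, power is 61%. So about 64% is a ceiling for any count distribution with these two figures, provided no more than 36% are affected on IHAT.
- Keeping 1.28 but taking the planned 25% affected is worse: 29% under a negative binomial.

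**4. Keeping Poisson and lowering the mean.**
- Matched to 36%: mean = −ln 0.64 = 0.446; SE = 0.159; power 55%.
- Matched to 25%: mean = −ln 0.75 = 0.288; SE = 0.198; power 44%.

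**5. Check on H3.** With 25% against 15%, 200 per arm and one-sided 10%, power is 89%, as the protocol says. The problem is confined to H2.

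**The case against.** The strongest reply is that the protocol does not say the two HIGH figures count the same thing. The 36% is of episodes recorded as adverse events. The 1.28 carries no stated capture route, and this trial itself collects diarrhoea both by questionnaire and on adverse-event forms. Alternatively, 1.28 may be a mean per affected child. That is an assumption, but a plausible one: a Poisson mean of 0.446 gives 0.446/0.36 = 1.24 episodes per affected child. The mean per child would then be 0.36 × 1.28 = 0.46, the variance about 1.07 times the mean, and there would be almost no overdispersion.

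This stands as an objection to diagnosing heavy overdispersion, but it does not rescue the 90%. At a mean of 0.46, SE = √[(1/0.4608 + 1/0.3686)/200] = 0.156 and power is 56%, or about 54% with the factor 1.07.

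It is also fair that 200 per arm was chosen for the efficacy non-inferiority test, that H2 power is described as something this size also provides, and that the trial is called a pilot with re-testing to follow. That limits the consequences; it does not make the stated figure right.

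A reader might also infer that Section 8.2 wrongly applies logistic regression to a count. The sentence there is brief, can be read as the same strata adjustment and Wald test, and defers to an analysis plan not shown. It is context, not a separate fault.

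**Conclusion.** The point holds: the 90% stated for H2 is contradicted by figures in the same section. Power at a rate ratio of 0.8 is about 40–55% on the reconciliations that fit a specific model: 39% and 51–54% if 1.28 and 36% describe the same children, 44–55% if the mean is lowered under Poisson. Its upper limit is about 64% with both figures kept. All values assume 200 analysed children per arm and a one-sided 10% Wald test.

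Several stronger conclusions are tempting but not supported:
- *That 39–54% is the true power.* These are results of two chosen models; the documents do not fix the distribution.
- *That the counts are shown to be heavily overdispersed.* The mean itself may be wrong.
- *That superiority would be falsely claimed in 20–30% of null trials.* This needs both overdispersion and an uncorrected Poisson analysis, and no section prescribes the latter.
- *That only a rate ratio near 0.56 is detectable with 90% power.* That is the negative binomial value alone.

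**What to change.** In Section 8.1:
1. Say what the 1.28 and the 36% each measure (children, event, capture route, per child or per affected child), and reconcile them with each other and with the planned 25%.
2. State the variance or overdispersion assumption for the count.
3. Replace the 90% and almost 90% for H2 by the recomputed figure. On present information this is about 40–55% for a 20% reduction, and not above about 64%.

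As a supporting change, when the H2 analysis is specified, name a count model robust to overdispersion (negative binomial, or Poisson with robust variance), with the randomisation strata and a log(observed time) offset, since 15% non-completion is expected.

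The cost is wording, a query to the holders of the HIGH data, and a less favourable stated power. No extra children or data are needed, and H2 can remain a primary hypothesis.

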## II. POWER of the trial for the secondary endpoints

1) Microbiome (Enterobacteria log10 counts):

We based our calculation on the data for Enterobacteria (the genus that contains most enteropathogens including *E. coli*) reported in Zimmermann 2014 study conducted with 4 months supplementation (8): with iron 8.9 (0.3) and without iron 8.0 (0.4). Taking into consideration that in this study the analysis combined the groups with 2.5 mg Fe and 12.5 mg Fe MNP, then the combined sample size implies an individual standard deviation of 3 for the Enterobacteria and assuming a 0.9 difference between the groups and a superiority margin of 0.2 (i.e. an absolute difference in Enterobacteria between the IHAT and ferrous sulphate arms of - 0.2), the sample size of 200 children per group would give us 85% (at 10% one-sided significance level).

2) Calprotectin

Again, we based this calculation in the Zimmermann 2014 study (8). Calprotectin concentration with iron: 248.9 +/- 2.2 µg/g and without iron: 102.5 +/- 2.2 µg/g in the 12.5 mg MNP. Here the individual SD should be around 11.8 considering the study sample size in the 12.5mg Fe MNP group, which would mean that with 200 per arm we could detect an absolute mean difference of 3 with 90% power (10% one-sided sig level) and with 50 per arm we would be able to detect a mean difference of 6.1.

3) NTBI

For this calculation we have used the 'normal serum' data provided by [name] with the same method we intend to use in the study (44). Taking the values reported in the paper for 'normal serum' of 0.24 +/- 0.15 (mean +/- SD), n=9 range 0.04 – 0.41, the individual standard deviation would be 0.45. There is no published data with this method for NTBI after an iron dose so we have assumed we would like to detect a mean difference of 0.5 between the IHAT and the ferrous sulphate arm, which would mean that with 50 per arm the power would be more than 90%. To be able to detect smaller differences with this method we would need to increase sample size.

## 8.2 Statistical analysis

The data analysis plan will be fully developed prior to database lock and will be done with the expert input from [name] of the MRC Biostatistics Unit in Cambridge. Briefly, for the primary analysis, we will fit a logistic regression to the efficacy outcome data, adjusting for the strata created by age and Hb level groups prior to enrolment. The odds ratio for effect of IHAT relative to ferrous sulphate will be estimated, and if the lower 90% one-sided confidence interval is above 0.583 (equivalent to the 10% non-inferiority margin above), non-inferiority will be declared for IHAT. The diarrhoea endpoint will be analysed in a similar way, but tested for superiority (i.e. if the one-sided p-value for the Wald test of the effect of IHAT is less than 0.1) for the comparison between IHAT and ferrous sulphate. For the primary non-inferiority hypothesis we will conduct per-protocol and intention-to-treat analyses and for the superiority hypotheses we will conduct intention-to-treat analyses.

The secondary endpoints (calprotectin, NTBI etc) will be tested using linear regression with the same covariates. Morbidity data will be analysed using multiple regression analysis controlling for possible confounders.

In relation to the microbiome data analysis we will work together with our collaborators in the Sanger Institute and use the most up to date bioinformatics methodology available at the time of data analysis to investigate the impact of treatment arm and time in the composition of the gut microbiome. Since this analysis will only occur in late 2018/early 2019, it is premature to decide the strategy for data analysis now as this is a fast moving field with new and better bioinformatics tools becoming available every couple of months. The Sanger Institute works very closely with the European Bioinformatics Institute (EBI) (housed in the same campus) to ensure they use the very latest tools in their microbiome analysis.

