**All outcome measures will be assessed at 0, 2 and 12 weeks in all the children.**

**The 2 weeks time-point will provide an indication of acute compound-related effects and the 12 weeks time-point of chronic (i.e. longer term/chronic) effects.**

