### **3 Study design**

#### **3.1 Type of study and design**

3-arm, parallel, randomised, placebo-controlled, double blind.

Children will be randomised (1:1:1) to IHAT, ferrous sulphate or placebo, each arm will include an intervention period of 12 weeks, faecal and blood samples will be collected at the time-points indicated below.

[figure not shown]

Participants will be iron deficient anaemic young children (n=705, accounting for 15% loss to follow-up) living in rural communities in the Upper River Division in The Gambia. Children will be recruited and randomised into the 3 study arms (n=235 per arm). Inclusion criteria will be: apparently healthy as judged by a study nurse on the day of recruitment, age 6-35 months, no malaria (RDT negative) and IDA defined as  $7 \leq \text{Hb} < 11$  g/dl (for recruitment we will use Medonic Hb values rather than HemoCue) with serum ferritin < 30 µg/L.

Each arm will include an intervention period of 12 weeks. As suggested by our BMGF proposal reviewers, we have included a placebo arm to allow us to fully evaluate IHAT effects, particularly to rule-out negative impact on diarrhoea episodes, the gut microbiome and compound-related

bacterial infection, and to determine treatment effect sizes with either IHAT and ferrous sulphate that will be necessary to power future iron supplementation studies (please refer to Section 11.1.1.).

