## **3.2 Randomisation and blinding procedures**

### **3.2.1 Randomisation**

Recruited children (N=705) will be randomly assigned (computer generated) to receive one of the 3 treatment arms (N=235 in each arm) stratified by the Hb concentration prior to enrolment and age. This will assure that Hb concentration at baseline (as a proxy for erythropoietic demand, which is the main driver for iron absorption) will not differ between the 3 arms.

At recruitment, each child will be categorised into two Hb classes (below or equal to/above the median Hb for that recruited cohort) and also according to age into 3 classes (6-11 months, 12-23 months and 24-35 months). This will divide children into 6 different strata and in each strata the children will be randomly assigned to one of the 3 treatment arms using a computer program and a block randomisation approach with fixed block size by age and Hb levels as defined above.

Ideally subjects will be recruited so that there will be balanced numbers in each of the 3 age classes; each of the age classes are further categorised into two groups based on the Hb level. Thus, in the balanced case, a total of 117-118 subjects each will belong to one of the six strata, created by Hb level (Low, High) and age group (Young, Middle, Old) combinations:

- a. Low Hb, young age group
- b. Low Hb, middle age group
- c. Low Hb, old age group
- d. High Hb, young age group
- e. High Hb, middle age group
- f. High Hb, old age group

However, 204 random treatment allocations will be generated for each strata in order to allow flexibility with respect to the numbers recruited in each of the six groups (a)-(f). That is, the list of treatment sequences in the balanced case will be extended by 86-87 to account for imbalance in the ages of children enrolled in the study as it may not be possible due to the age demographics of the study communities to enrol equal numbers in each of the age classes above. In any case, we will ensure that equal numbers within each strata are assigned to one of the treatment arms. This will be based on a pre-specified list of IDs ranging from 001-204, 205-408, 409-612, 613-816, 817-1020 and 1021-1224 for groups (a)-(f) above, respectively.

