Prior to enrolment (Day 0), which will be a maximum 4 weeks after the screening visit, eligible children will be taken back to the clinic for a finger prick to confirm absence of malaria by RDT and haemoglobin concentration by hemocue. Children will be called back in clusters of 58-60 on a Monday, Tuesday, Wednesday and Thursday. This is necessary before they can be enrolled and randomised to the study because of the time it takes to get all the screening results back from the labs for all children in that cohort (i.e. around 4 weeks). On the Friday of the same week, the list of all the children that remain RDT negative and with  $7 \leq \text{Hb} < 11$  g/dL will be sent to the

study statistician who will run the randomisation to one of the three study arms, stratified by Hb and age as described in 3.2.1., and send the list with the study IDs to the PIs that same day.

The week after, children will be taken back to the clinic again in the same cluster (i.e. either on the Mond, Tue, Wed or Thur as per their Day 0 cluster) and this will be their study Day 1 (see below).

We will enrol children in 3 cohorts (n=235 children each) that will run sequentially.

Each study cohort will be organised as follows. Each cohort will have 4 clusters (58-60 children per cluster), children in each cluster will be allocated to one of the study health facilities according to the child's compound proximity to each of the 4 study health facilities. Children in the first cluster will all have their study visits on a Monday, children in the second cluster will all have their study visits on the Tuesday, and the third cluster on the Wednesday and fourth cluster on the Thursday. Children in each cluster will also have their weekly check-ups at the study health facility on the same day of the week and would have had their Day 0 visit on the same day of the week.

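### Continuous secondary markers are regressed on the age by Hb strata alone; adding each marker's Day 1 value and a cohort term would recover precision from data already collected

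*Supplement*

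**What the plan says.** Section 8.2 fits the primary logistic model "adjusting for the strata created by age and Hb level groups prior to enrolment". It then states: "The secondary endpoints (calprotectin, NTBI etc) will be tested using linear regression with the same covariates". The secondary covariate set is therefore the six strata formed by two Hb classes and three age classes.

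Section 3.2.1 defines the Hb classes as "below or equal to/above the median Hb for that recruited cohort", so the boundary moves from cohort to cohort. Section 5.1.2 says: "We will enrol children in 3 cohorts (n=235 children each) that will run sequentially". Appendix 1 dates the three intervention periods 8 January to 5 April, 23 April to 19 July and 6 August to 1 November 2018. Cohort is not named as a covariate.

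On measurement, section 2.1 says: "All outcome measures will be assessed at 0, 2 and 12 weeks in all the children". Sections 5.1.3 and 5.2.2 confirm that venous blood and stool are taken on days 1, 15 and 85.

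Three other statements in section 8.2 limit the point. Morbidity models will control for confounders that are not listed. The microbiome strategy is deferred. The full data analysis plan, which is not among the documents, is to be completed before database lock.

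**The concern.** For a continuous marker measured before and after treatment, its own pre-treatment value is usually the strongest available predictor of the later value. A randomised comparison that leaves it out carries more residual variance than it needs to. Here the baseline sample has already been drawn and assayed, so the covariate costs nothing further.

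Cohort is a second omitted source of variance. Randomisation is run cohort by cohort, the low-Hb class refers to different Hb levels in different cohorts, and the cohorts fall in different parts of the year. Sections 1.4.1 and 11.1.3 place the malaria peak in October and November, and cohort 3 runs through October. Inflammatory and iron markers could plausibly shift with season, although the documents do not quantify this.

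At stake is the precision of the secondary comparisons on gut inflammation and iron handling. Section 8.1 also says the trial should supply estimates for a later pivotal study, so narrower intervals matter even where power is adequate.

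**Working it through.** **Inputs (sections 3.1 and 8.1).** Allocation is 1:1:1, with 200 evaluable children per arm, tested "at a 10% one-sided significance level" (z = 1.2816).
- Calprotectin: SD 11.8 µg/g, difference 3 µg/g, stated power 90%.
- Enterobacteria: SD 3 log10, difference 0.9 with superiority margin 0.2 (net 0.7), stated power 85%.
- NTBI: SD 0.45, difference 0.5, stated power above 90% with 50 per arm.

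The SDs are taken as the protocol gives them.

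**Step 1: reproduce the plan's figures.** Power = Φ(δ / (SD·√(2/n)) − 1.2816).
- Calprotectin: 3 / (11.8 × 0.1) = 2.542; less 1.2816 is 1.261; power 89.6% (stated 90%).
- Enterobacteria: 0.7 / (3 × 0.1) = 2.333; less 1.2816 is 1.052; power 85.4% (stated 85%).
- NTBI, 50 per arm: 0.5 / (0.45 × 0.2) = 5.556; less 1.2816 is 4.274; power above 99.9%.

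The calculations use the full SD and take no credit for any covariate.

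**Step 2: add the Day 1 value.** Residual variance becomes SD²·(1 − ρ²), where ρ is the Day 1 to Day 85 correlation remaining after the strata. The equivalent sample size is 200/(1 − ρ²), and the interval shrinks by 1 − √(1 − ρ²). The documents give no ρ, so a range is assumed.

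| ρ | 1 − ρ² | 200 per arm worth | Interval narrower by | Calprotectin power | Enterobacteria power |
|---|---|---|---|---|---|
| 0 | 1.00 | 200 | 0% | 89.6% | 85.4% |
| 0.2 | 0.96 | 208 | 2.0% | 90.5% | 86.4% |
| 0.3 | 0.91 | 220 | 4.6% | 91.7% | 87.8% |
| 0.4 | 0.84 | 238 | 8.3% | 93.2% | 89.7% |
| 0.5 | 0.75 | 267 | 13.4% | 95.1% | 92.1% |
| 0.6 | 0.64 | 313 | 20.0% | 97.1% | 94.9% |

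The calprotectin difference detectable with 90% power falls from 3.02 to between 2.96 (ρ = 0.2) and 2.42 (ρ = 0.6). The Enterobacteria column applies only if that endpoint is analysed by the section 8.2 regression.

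**Step 3: add cohort.** If cohort alone explained an assumed 2%, 5% or 10% of the variance, Enterobacteria power would move from 85.4% to 85.9%, 86.7% or 88.1%.

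**Step 4: test whether the primary efficacy model would also gain.** Trials were simulated with 200 per arm, true odds ratio 1, about 30% response and the fixed margin of 0.583, with 1,500 runs in each of four scenarios for the strength of baseline Hb and cohort effects. Power was 0.84-0.88 with the strata alone and 0.80-0.87 with cohort and continuous Hb added. In a logistic model, prognostic covariates enlarge the standard error of the conditional log odds ratio, while the true odds ratio and the margin stay put. There is no gain.

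**The case against.** The strongest reply is that section 8.2 is a summary, that the full analysis plan is still to be written, and that covariate lists normally belong there. That would settle the matter if section 8.2 were silent. It is not: it specifies the covariates of the secondary models by reference to the strata. The open plan does mean that the change can still be pre-specified.

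A second reply is that power is not short. This largely stands. NTBI is near 100% for its assumed difference, and calprotectin reaches 90% for a difference of 3, when the cited data differ by 248.9 − 102.5 = 146.4 µg/g. The case rests on precision, not on rescuing an underpowered endpoint.

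A third is that ρ may be low. Section 5.1.3 treats hepcidin and NTBI as fast-moving, and section 11.1.1 describes the microbiome at this age as unstable. That is why the range starts at 0.2, where Enterobacteria power gains only one percentage point.

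A reader might also infer more than the documents support:
- That the comparison is biased, or that the moving Hb cut breaks the stratification. Randomisation in blocks within strata, run cohort by cohort, protects the comparison, and a cohort-relative cut is a legitimate stratifier.
- That the primary efficacy test would gain from continuous Hb. Step 4 shows no gain. Reporting a standardised risk difference beside the odds-ratio rule would also leave open which of the two governs.
- That the diarrhoea outcomes lack baseline adjustment. They accrue over follow-up and have no Day 1 value, and current moderate-severe diarrhoea is an exclusion.
- That no model allows for season. The morbidity models may, through their unlisted confounders.

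**Conclusion.** The point holds for the continuous secondary endpoints that section 8.2 assigns to linear regression. The stated model omits each marker's Day 1 value and omits cohort, although both are available for the trial. The loss is one of precision; validity and the stated powers are unaffected.

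Its size depends on a correlation the documents do not give. Between 0.2 and 0.6 it ranges from trivial (4% of residual variance) to substantial (36%). If the strata already carry part of the baseline information, the gain is smaller. The cohort contribution is likewise assumed, at roughly 0.5 to 3 power points. Calprotectin is the cleanest example, being named for this regression; the Enterobacteria figures are conditional on the deferred microbiome strategy. This is a worthwhile improvement at almost no cost, not a correction of an error that endangers the trial.

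**What to change.** In section 8.2, and in the full analysis plan before database lock and unblinding:
1. Add the Day 1 value of the same marker to each continuous secondary model, on the log scale where the marker is skewed, with simple imputation where it is missing. Section 5.1.3 allows stool within 7 days of the time-point, so state that a sample taken after the first dose does not count as a baseline.
2. Add cohort (three levels) to the same models, alongside the existing strata.
3. Optionally, add cohort to the diarrhoea models comparing IHAT with ferrous sulphate. The benefit there is not quantified.

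Leave the primary efficacy model and its odds-ratio margin unchanged.

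The cost is a line or two of text, a few degrees of freedom, and an imputation rule for missing baselines. No new data are needed, and fixing the covariates in advance avoids choosing them after the results are known.
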